### Conversion from MIPD to OPD

Any incision used for other reasons than trocar placement and specimen extraction is defined as a conversion. Patients allocated to MIPD but converted to OPD will still be analyzed in the MIPD group, according to the intention-to-treat principle. Reasons for conversion will be registered and categorized as urgent or non-urgent conversions [18].

### Blinding

Within the DIPLOMA-2 trial, it was not deemed possible to blind the assessors of the primary outcome, due to logistical reasons. Therefore, an independent adjudication committee, blinded for treatment allocation, will assess the primary outcome of all included patients. Furthermore, regarding the most important secondary outcome, time to functional recovery, patients will be blinded for treatment allocation pre-operatively, until 5 days after surgery. Directly after skin closure, while the patient is still under general anesthesia, the patients will receive a firmly taped, large 40 × 40 cm abdominal dressing to cover their incision(s), and therefore, their treatment allocation will remain blinded (minimally invasive or open). This abdominal dressing will be removed at postoperative day 5, or earlier when all criteria for functional recovery are met, or for medical reasons, such as suspicion of wound infection. If earlier inspection is required, attempts are made to maintain patient blinding. This blinding has proven to be successful in previous multicenter RCTs [19–21]. The success of blinding will be assessed using the blinding index as proposed by Bang et al. [22] Patients will be asked on day 2 and before removal, about the alleged treatment allocation, based on five categories: (1) strongly believe it was MIPD, (2) somewhat believe it was MIPD, (3) do not know, (4) somewhat believe it was OPD, (5) strongly believe it was OPD. Patient blinding will not be performed in patients who are intra-operatively diagnosed with irresectable disease, such as metastases. Since patient blinding only influences one of the secondary outcomes, time to functional recovery, and not the primary outcome, this is considered of minor influence. Sensitivity analysis, excluding patients with perioperative diagnosed metastasized disease, will be performed for analysis of time to functional recovery.

### Primary outcome

The primary outcome is the Comprehensive Complication Index (CCI®), measured up to 90 days post-operatively. The CCI® score is developed to reflect the postoperative morbidity based on the Clavien-Dindo classification of postoperative complications and is validated for pancreatic surgery [23–25]. The CCI® score ranges from 0 (no complication of any kind during the postoperative period) and 100 (death of patient). The advantage of the CCI® over the Clavien-Dindo classification is the ability to accumulatively assess the postoperative morbidity considering all complications instead of only scoring the “most severe” complication. Repeat Clavien-Dindo 1 complications will be counted only once (i.e., not be scored cumulatively) in the CCI.

### Secondary outcomes

The most important secondary outcome is postoperative time to functional recovery. Functional recovery, as defined by a previous RCT [19, 20], is reached when all of the following criteria are met: (I) adequate pain control with oral analgesia only; (II) restoration of mobility to an independent level (or to preoperative level if previously impaired); (III) ability to maintain sufficient caloric intake (minimum of 50% required calories); (IV) absence of intravenous fluid administration; (V) no signs of active infection (no fever, decreasing C-reactive protein below 150 mg/L).

Post-operative activity will be measured using a Fitbit™ Inspire 2, by patients on their wrists (1–2 weeks) from prior to surgery to 90 days after surgery [26–29]. A comprehensive overview of the outcomes of the postoperative activity tracking will be described as a separate publication.

Other secondary outcomes of this trial include intra-operative parameters (type of surgery (laparoscopic or robot-assisted), conversion (urgent or non-urgent), method of anastomosis, vessel resection, operative time, blood loss, and blood transfusion), postoperative outcomes (up to 90 days after surgery; major complications (defined as a Clavien-Dindo grade III or higher) and mortality (and whether related to surgery), postoperative pancreatic fistula [30], post-pancreatectomy hemorrhage [31], delayed gastric emptying [32], chyle leak [33], surgical site infection [34], postoperative intervention (surgical, radiologic or endoscopic), intensive care unit admission, (multi) organ failure, length of hospital stay, readmission, (time to) start of adjuvant therapy) and pathological outcomes (pathological diagnosis, tumor size, histology and tumor grading [35], distance from the tumor to all margins, number of retrieved lymph nodes, number of positive lymph nodes, lymphovascular and perineural tumor invasion, and venous and arterial tumor involvement). For the economical evaluation, costs (intra-operative and postoperative costs (up to 90 days)) and quality of life (using the validated EQ-5D-5L, QLQ-C30, and PAN-26 questionnaires with additional questions regarding scar complications and body image (up to 3 years)) are compared [36, 37].

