**Methods/design:**

The DIPLOMA-2 trial is an international randomized controlled, patient-blinded, non-inferiority trial performed in 14 high-volume pancreatic centers in Europe with a minimum annual volume of 30 MIPD and 30 OPD. A total of 288 patients with an indication for elective pancreatoduodenectomy for pre-malignant and malignant disease, eligible for both open and minimally invasive approach, are randomly allocated for MIPD or OPD in a 2:1 ratio. Centers perform either laparoscopic or robot-assisted MIPD based on their surgical expertise. The primary outcome is the Comprehensive Complication Index (CCI®), measuring all complications graded according to the Clavien-Dindo classification up to 90 days after surgery. The sample size is calculated with the following assumptions: 2.5% one-sided significance level (α), 80% power (1-β), expected difference of the mean CCI® score of 0 points between MIPD and OPD, and a non-inferiority margin of 7.5 points. The main secondary outcome is time to functional recovery, which will be analyzed for superiority. Other secondary outcomes include post-operative 90-day Fitbit™ measured activity, operative outcomes (e.g., blood loss, operative time, conversion to open surgery, surgeon-reported outcomes), oncological findings in case of malignancy (e.g., R0-resection rate, time to adjuvant treatment, survival), postoperative outcomes (e.g., clinically relevant complications), healthcare resource utilization (length of stay, readmissions, intensive care stay), quality of life, and costs. Postoperative follow-up is up to 36 months.

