### Data collection and patient follow-up

Baseline characteristics (age, sex, performance status (Karnofsky score [38]), ASA physical status, body mass index, previous abdominal surgery, preoperative diabetes mellitus, preoperative imaging conclusion including tumor size and involvement of other organs and vessels, neo-adjuvant treatment, serum levels of Hba1C, CA 19.9 and CEA, and baseline quality of life questionnaires’ scores will be recorded before intervention. All required clinical data will be collected after randomization (i.e., from hospitalization up to 36 months postoperatively) using standardized online case report forms by the local treating physicians and will be crosschecked with source data by the study coordinators at 3 and 36 months after the last patient is enrolled. To assess postoperative daily activity (up to 90 days), this study uses the Fitbit™ Inspire 2 to record step counts (as a measure of physical activity), and heart rate, combined as “active minutes” per day. For quality-of-life measurements, the validated questionnaires will be sent (electronically) to participating patients at baseline and at 1, 3, 6, 12, and 36 months after surgery. Patients will also receive an additional questionnaire at 6 months focusing on possible complications with the scar and body image. Patients will be followed at the outpatient clinic according to local protocols (including abdominal CT scan and serum levels of CA 19.9 and CEA tumor markers, if indicated). In each center, a monitor visit is performed 90 days after the last included patient has undergone surgery to cross-check primary and secondary outcome data.

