The primary outcome measure “CCI®” will be expressed as means (standard deviations) or medians (interquartile ranges) and will be tested for non-inferiority using independent samples *t*-test or Mann–Whitney *U* test, as appropriate dependent of the distribution. The most important secondary outcome measure “time to functional recovery” will be measured in days and will be tested for superiority using the Wilcoxon (Gehan-Breslow) test or log-rank test, depending on the distribution. Secondary analysis will include correction for censored patients (death before time to functional recovery obtained). For the primary study outcome, the lower limit of the two-sided 95% confidence interval of the difference in proportions will be reported and compared with the non-inferiority margin. Additionally, the individual functional recovery criteria will be analyzed separately. Major complications, expressed in proportions, will be tested for non-inferiority using chi-square or Fisher’s exact test as appropriate. The distribution of variables will be determined using several plots (boxplot, Q-Q plot and histogram) and the Kolmogorov–Smirnov and Shapiro–Wilk tests. For comparison of normally distributed continuous variables, the independent samples *t*-test will be used, and values will be expressed as means (standard deviations). Continuous non-normally distributed variables will be compared using the Mann–Whitney *U* test, and values will be expressed as medians (interquartile ranges). Categorical variables will be compared by chi-square or Fisher’s exact test as appropriate, and values will be expressed as proportions. A two-tailed *p*-value < 0.05 will be considered statistically significant. Time to event endpoints, such as survival, will be calculated using Kaplan–Meier estimations. A Cox regression analysis will be performed to investigate predictors of postoperative survival. All parameters with a *p*-value < 0.1 in a univariable analysis will be included in the multivariable Cox regression analysis. Additionally, multivariable analyses will be performed to determine predictors for primary and secondary study outcomes, for example the occurrence of major complications, postoperative pancreatic fistula, and R0 resection. Furthermore, predictors for receiving adjuvant chemotherapy or readmission will be assessed.

For subjects who are lost to follow-up, a sensitivity analysis will be performed to determine best case/worst case scenarios.

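### The general two-sample rule makes no use of a baseline; if applied to Fitbit activity, which is recorded from before surgery, it gives an unbiased but less precise comparison than a baseline-adjusted one.

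*Protocol article*

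**What the plan says.** The abstract names tracker activity as a secondary outcome: "Other secondary outcomes include post-operative 90-day Fitbit™ measured activity". The Secondary outcomes section states: "Post-operative activity will be measured using a Fitbit™ Inspire 2, by patients on their wrists (1–2 weeks) from prior to surgery to 90 days" after the operation. It then adds: "A comprehensive overview of the outcomes of the postoperative activity tracking will be described as a separate publication".

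Data collection and patient follow-up gives the measures. The device is to "record step counts (as a measure of physical activity), and heart rate", and these are combined into active minutes per day. That section does not list activity among the baseline characteristics, and it describes the device as a means of assessing activity after surgery.

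The Statistical analysis section gives one general rule for comparing continuous variables. On one branch, "For comparison of normally distributed continuous variables, the independent samples *t*-test will be used". On the other, "Continuous non-normally distributed variables will be compared using the Mann–Whitney" U test. Neither branch has a covariate, and no exception is made for outcomes with a pre-operative value. The multivariable models in the same section look for predictors of outcome; they are not adjusted comparisons of the two arms. A detailed analysis plan is promised before database lock of the outcomes up to 90 days.

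**The concern.** Habitual activity can differ widely between patients for reasons unrelated to the operation. A two-sample test on post-operative values leaves that variation in the error term. A model that includes each patient's own pre-operative level removes the part that the baseline explains, and it corrects for chance imbalance in that level. Randomisation is stratified by technique, fistula risk and indication, so nothing in the design balances pre-operative activity directly.

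What is at stake is precision on a secondary outcome. The recovery hypothesis itself rests on time to functional recovery, whose five criteria do not include tracker activity. The Fitbit data are supporting, device-recorded evidence on the same question, and a wider interval makes that evidence weaker than it need be.

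**Working it through.** **Inputs from the protocol article.** Randomised: 192 MIPD and 96 OPD. Per-protocol: 159 and 88 (Sample size calculation). The article gives no standard deviation, effect size, interval width or correlation for activity, so results are in standard deviation (SD) units and r is an assumption shown over a range.

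**The plan's own counts.** Apply the stated losses multiplicatively, with conversion in the MIPD arm only:

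- MIPD: 192 × 0.95 × 0.90 × 0.97 = 159
- OPD: 96 × 0.95 × 0.97 = 88

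These match the stated 159 and 88. With margin 7.5, SD 20 and one-sided 2.5%, the power for the primary outcome is 80.6% (normal) or 80.3% (noncentral t), against 80% stated. The counts can therefore be used here.

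**Unadjusted interval.** The 95% half-width is 1.96 × √(1/n₁ + 1/n₂) SD.

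- 159 vs 88: 1.96 × √(1/159 + 1/88) = 0.260 SD
- 192 vs 96: 1.96 × √(1/192 + 1/96) = 0.245 SD

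**Adjusted interval.** With a baseline that treatment cannot have affected, ANCOVA multiplies the variance by 1 − r², and so the interval width by √(1 − r²). The equivalent unadjusted sample size is 288/(1 − r²).

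| Assumed r | Variance factor 1 − r² | Width factor | Narrowing | Half-width, 159 vs 88 (SD) | Half-width, 192 vs 96 (SD) | Equivalent N for 288 |
|---|---|---|---|---|---|---|
| 0.2 | 0.96 | 0.980 | 2% | 0.255 | 0.240 | 300 |
| 0.3 | 0.91 | 0.954 | 5% | 0.248 | 0.234 | 316 |
| 0.5 | 0.75 | 0.866 | 13% | 0.226 | 0.212 | 384 |
| 0.7 | 0.51 | 0.714 | 29% | 0.186 | 0.175 | 565 |

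**Cost if r is small.** Adjustment uses one residual degree of freedom: 245 becomes 244 at 247 patients. Little is lost if the baseline proves uninformative.

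**Change scores.** A two-sample test on change from baseline would fit the general rule and would use the baseline. With equal variances before and after surgery, its variance factor is 2(1 − r): 1.6, 1.4, 1.0 and 0.6 at the four values of r. It is worse than ignoring the baseline below r = 0.5, no better at 0.5, and at every r in the table less efficient than ANCOVA, since 2(1 − r) − (1 − r²) = (1 − r)², which is positive for r below 1.

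**Scope.** These widths apply to the t-test route. On the Mann–Whitney route the article specifies no interval for a mean difference, so the percentages do not carry over directly.

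**The case against.** The strongest reply is that the article never chooses an analysis for Fitbit activity. The Statistical analysis section does not mention steps or active minutes, and it does not say that post-operative values are compared alone. A change score would comply with the rule. The activity results go to a separate publication, and an analysis plan that is not shown may already adjust. Covariates for a secondary device outcome are the sort of detail a condensed article may leave to those documents.

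Most of this stands. A reader might infer that the plan discards the pre-operative data and is bound to report too wide an interval. The documents do not support that: the loss arises only if the general rule is applied to post-operative activity, and its size needs an r that is not given. The correlation may also differ between the days in hospital and day 90. Nor is the unadjusted comparison biased; chance imbalance in pre-operative activity is ordinary sampling variation that its interval already covers.

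The baseline is also less well described than one would like. The bracketed 1–2 weeks could refer to the length of pre-operative wear or to something else, and completeness is not stated.

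What does not stand is that nothing remains to be said. The article does fix a general rule for continuous variables. That rule makes no use of a baseline, and the device is stated to be worn from before surgery. A better method is available at almost no cost.

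**Conclusion.** The point holds as a conditional improvement. If the general rule for continuous variables is applied to post-operative Fitbit activity, the comparison is valid but less precise than the recorded data could make it. The likely gain runs from negligible (about 2% narrower at r = 0.2) to substantial (about 29% at r = 0.7). At r = 0.5 it equals one-third more patients, 384 against 288.

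This rests on three assumptions: the t-test route, a usable pre-operative record in most patients, and the assumed range of r. It affects only the precision of a secondary outcome. The primary outcome, the 288 patients and the 80% power are unaffected. The priority is low, and confidence is moderate because the analysis plan is not shown.

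**What to change.** State in the analysis plan, before database lock, and apply equally to the separate activity publication:

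- Post-operative activity (mean daily steps and mean daily active minutes, each over defined periods) is compared between arms by ANCOVA, or by a mixed model for repeated periods, with the patient's own pre-operative mean as covariate.
- The adjusted MIPD–OPD difference is reported with its 95% confidence interval.
- The pre-operative window and the minimum wear that counts as a baseline are defined.
- Patients without pre-operative wear are kept in the analysis by a simple rule fixed in advance: mean imputation of the baseline or a missing-baseline indicator.

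The Randomization section places randomisation after consent at the outpatient clinic, so some pre-operative wear may follow allocation. Patients are blinded to allocation before surgery (Blinding), so the pre-operative value remains a valid covariate in that case.

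The cost is wording only. No extra data are needed beyond the recording already planned, and the sample size does not change. Fixing the rule before lock also prevents a later adjustment from looking data-driven.

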### Data collection and patient follow-up

Baseline characteristics (age, sex, performance status (Karnofsky score [38]), ASA physical status, body mass index, previous abdominal surgery, preoperative diabetes mellitus, preoperative imaging conclusion including tumor size and involvement of other organs and vessels, neo-adjuvant treatment, serum levels of Hba1C, CA 19.9 and CEA, and baseline quality of life questionnaires’ scores will be recorded before intervention. All required clinical data will be collected after randomization (i.e., from hospitalization up to 36 months postoperatively) using standardized online case report forms by the local treating physicians and will be crosschecked with source data by the study coordinators at 3 and 36 months after the last patient is enrolled. To assess postoperative daily activity (up to 90 days), this study uses the Fitbit™ Inspire 2 to record step counts (as a measure of physical activity), and heart rate, combined as “active minutes” per day. For quality-of-life measurements, the validated questionnaires will be sent (electronically) to participating patients at baseline and at 1, 3, 6, 12, and 36 months after surgery. Patients will also receive an additional questionnaire at 6 months focusing on possible complications with the scar and body image. Patients will be followed at the outpatient clinic according to local protocols (including abdominal CT scan and serum levels of CA 19.9 and CEA tumor markers, if indicated). In each center, a monitor visit is performed 90 days after the last included patient has undergone surgery to cross-check primary and secondary outcome data.

### Quality and safety

A minimum annual center volume of at least 30 MIPD and 30 OPDs was set as requirement for participating in the DIPLOMA-2 trial. By using this volume requirement, we aim for centers to maintain an annual volume of at least 20 MIPD during the trial, despite randomization [14]. Centers will participate for either L-MIPD or R-MIPD, depending on their main expertise. Surgeons are allowed to participate in DIPLOMA-2 if they have a personal experience of at least 60 MIPDs and 60 OPDs in the past 10 years.

All MIPD surgeons will be required to have participated in an endorsed MIPD training program or otherwise are asked to send a recorded and anonymized video of a personal MIPD procedure performed, before the start of the trial, which will be evaluated by the study team. In addition, the MIPD procedures within the DIPLOMA-2 trial will be recorded and stored, to be available upon request of the study team.

All adverse events will be recorded up to 90 days postoperatively. Serious adverse events will be reported through a web portal (www.toetsingonline.nl) to the Dutch central committee on research involving human subjects (in Dutch: Centrale Commissie Mensgebonden Onderzoek (CCMO)) and the institutional review board (Medical Ethics Committee of Amsterdam UMC). The following serious adverse events must be reported to the study coordinator within 24 h: unplanned intensive care unit admission, any surgical intervention, readmission, and death (regardless of cause). The remaining adverse events are recorded in a yearly overview list. An independent data safety monitoring board (DSMB) is appointed to evaluate the study safety parameters. When each 50th included patient has completed 90 days of follow-up, the DSMB will meet (online) in order to assess the safety parameters. The DSMB exists of one independent statistician, one independent methodologist, one independent medical oncologist, and three independent surgeons. One of the DSMB members is appointed as chairman and a second member as secretary. The minutes of these meetings will be sent to the institutional review board of the study by the study coordinator and the trial steering committee. The DSMB will not be blinded and will be fully informed on all SAEs. The DSMB can request a full report of specific study outcomes whenever required. The study coordinator and principal investigator will only be present during the start (open discussion) of the DSMB meeting to provide the overall data and provide background information.

### Ethics

The DIPLOMA-2 trial will be conducted according to the principles of the Declaration of Helsinki (64^th^ version, October 2013) and in accordance with the local laws and regulations, such as in the Netherlands the Medical Research Involving Human Subjects Act. The local principal investigators are responsible to adhere to local laws and regulations. The independent ethics review board of the Amsterdam UMC (Amsterdam, the Netherlands; NL77750.018.21) and Provincial Ethic Committee Brescia (Brescia, Italy; NP4916) have approved the study protocol. Furthermore, approval from all local ethics committees of participating centers is obtained before participation in the study. The trial is registered in the ISRCTN registry: ISRCTN27483786.

